| (e) | Details of procedure and methodology proposed to be used (300 words) including description of the potential risks and benefits, exclusion and Inclusion criteria outcome measures, statistical analysis:  ***Patient population:*** *Covid-19 positive symptomatic cases either non-severe or severe category*  ***Intervention:*** *Two therapeutic interventions for non-severe category and three for severe category as described below*  ***Comparator:*** *Parallel arm design, compared among other interventional arm in same category*  ***Outcomes:*** *Clinical and laboratory improvements in 72 hours of treatment*  **Patient population-**  Patients diagnosed with SARS-CoV-2 infection after positive reverse-transcriptase–polymerase chain reaction (RT-PCR) assay.  **Inclusion criteria:**   1. Age ≥18 years at time of participation in the study 2. Laboratory (RT-PCR) confirmed infection with SARS-CoV-2 3. Symptomatic (severe or non-severe) Covid-19 disease 4. Willingness of study participant to accept randomization to any assigned treatment arm   **Exclusion criteria:**   1. Use of medications that are contraindicated with Lopinavir/Ritonavir, Hydroxychloroquine/Chloroquine, or Ribavirin and that cannot be replaced or stopped 2. Patient already on antiretroviral therapy with Lopinavir-Ritonavir based regimen or on Hydroxychloroquine/Chloroquine or on Ribavirin 3. Any known contraindication to test drugs such as retinopathy and QT prolongation 4. Known allergic reaction or inability to delivery oraly to Lopinavir-ritonavir, Hydroxychloroquine/ Chloroquine, Ribavarin 5. Pregnant or breastfeeding females 6. Receipt of any experimental treatment for 2019-nCoV (off-label, compassionate use, or trial related) within 30 days prior to participation in the present study or want to participate after enrolment   **Potential benefits:**   1. All those who participate in the trial will benefit from possible effective treatment for COVID-19 infection 2. The study will highlight the therapeutic options in management of the symptomatic patients of COVID-19 infection   **Potential risks:**  The present study will be conducted on symptomatic patients of COVID-19 attending AIIMS Rishikesh. The patients will be categorised based on severity and treatment will be allocated accordingly.  Adverse drug reactions, though not frequent may be associated with the treatment. Proper supportive management will be given to the patients at the institute.  **Methodology**:  **Flow Diagram**  Patients of COVID-19 infection - After confirmation by RT-PCR at AIIMS, Rishikesh  Screening for inclusion in trial Enrolment Excluded  ♦  Not meeting inclusion criteria  ♦  Declined to participate  ♦  Other reasons  Categorisation based on severity of patient  **SEVERE group**  **NON-SEVERE group**  Randomisation to treatment arm:  **A. Standard Treatment (ST-S)**  **B. Hydroxychloroquine + Ribavirin + ST-S**  **C. Lopinavir+ Ritonavir + Ribavirin + ST-S**  Randomisation to treatment arm:   1. **Standard Treatment (ST-NS)** 2. **Hydroxychloroquine + Ribavirin + ST-NS**  RandomisationAllocation Monitor progress of patient in 72 hours Follow-Up Patient improve- continue same treatment  Clinical evaluation- @72 hours  Improve - Continue same treatment  Progress – achieved end point and Shift to institute protocol for further treatment  Patient do not improve/ Signs of severe disease  Shift to **SEVERE group** treatment arms after randomization with new consent Analysis Analysis  **Total duration of observation**:  28 days from the time of enrolment into the study OR till patient is discharged or death whichever is longer  **Design:** Open label, Parallel arm design, stratified randomised controlled trial:  Patients will be screened for the study after diagnosis of COVID-19 infection by Microbiology team. Patients will be categorised as non-severe or severe based on predefined criteria. The patient will be enrolled in the study after a written informed consent. Since it is an exploratory trial as COVID-19 being a new disease, all patients who came under the purview of the inclusion criteria within the study period and who have consented for the study will be included. Clinical evaluations will be done by a separate investigator. Blinding will not be performed but dynamic randomization will be done. Patients will be followed up for a period of 28 days from the day of enrolment.  At the time of enrolment, demographic information will be collected from participants, and relevant data on their medical histories, comorbidities, and risk factors for severe COVID-19. It will be documented along with investigations including CBC, ECG, LFT, RFT, G6PD status.  The patients will be categorised as severe based on the following criteria:   - Confirmed pneumonia on chest imaging, SPo2 <93%, Pao_2_:Fio_2_ <300 mg Hg - Respiratory failure (need of mechanical ventilation) - Septic shock - Multiple (>2) organ dysfunction syndrome (MODS) - Liver disease (Child Pugh score ≥ C, AST>5 times upper limit) - Patients with known renal impairment (estimated glomerular filtration rate ≤30 mL/min/1.73 m2) or receiving continuous renal replacement therapy, haemodialysis, peritoneal dialysis - Other single organ failure (e.g. heart, pancreas, etc) if specific definition meets   Non-severe category includes mild and moderate disease severity category other than severe ones.  **Treatment Schedule**  **Non-severe Treatment arms (NS-group):**   \| **Treatment Arm** \| **Drug** \| \| --- \| --- \| \| A \| Standard Treatment (ST_NS_) \| \| B \| Hydroxychloroquine 400 mg twice on first day followed by 400 mg per oral daily for 10 days + Ribavirin (2.4 g orally as a loading dose followed by 1.2 g orally every 12 hours) for 10 days + Standard Treatment (ST_NS_) ^6^ \|   **Standard Treatment for non-severe cases (ST_NS_):**   1. Strict Isolation 2. Standard Precautions (Hand hygiene, Cough Etiquette, Wear surgical mask) 3. Hydration 4. Proper Nutrition 5. Supportive Pharmacotherapy (Antipyretic, Antiallergic, Cough Suppressant) 6. Treatment of Comorbid Diseases 7. Oseltamivir (75 mg BD) for patient who are tested positive for H1N1   If the patient improves clinically the same treatment will be continued. If the patient do-not improve or shows sign of severity (mentioned above) the patient will be shifted to the severity arm (S-group) of the clinical trial and again randomization will be done and enrolled after new consent only for severe group. However, if intervention falls on HCQ arm, then it will be taken as end point reached and shifted to institute treatment protocol for further management.  **Severe group Treatment arms (S-group):**   \| **Treatment Arm** \| **Drug** \| \| --- \| --- \| \| A \| Standard Treatment (ST_s_) \| \| B \| Hydroxychloroquine 400mg BD on day1 followed by 400 mg once daily + Ribavirin (2.4 g orally as a loading dose followed by 1.2 g orally every 12 hours) for 10 days + Standard Treatment (ST_s_) \| \| C \| Lopinavir(400mg) + Ritonavir (100mg) two tablets twice daily+ Ribavirin (2.4 g orally as a loading dose followed by 1.2 g orally every 12 hours) for 10 days + Standard Treatment (ST_s_)^6^ \|   **Standard Treatment for severe patients: (ST_s_)**   1. Strict Isolation 2. Standard Precautions (Hand hygiene, Cough Etiquette, Wear surgical mask) 3. Fluid Therapy 4. Supportive Pharmacotherapy (Antipyretic, Antiallergic, Cough Suppressant) 5. Oxygen supplementation (As required) 6. Invasive ventilation (As required) 7. Antibiotic agents for other associated infections (according to 2019 ATS/IDSA guidelines for non-ICU and ICU patients) 8. Vasopressor support 9. Renal-replacement therapy 10. Treatment of Comorbid Diseases 11. Oseltamivir (75 mg BD) for patient who are tested positive for H1N1   Patients will be assessed for clinical and laboratory improvements in 72 hours of treatment. In case the patient does not respond to the current treatment regimen the patient will be shifted to institute protocol for current practice of treatment.  **Timelines of investigations: Repeated at 72hrs interval**   \| Investigations \| Baseline \| Next 72hrs \| \| --- \| --- \| --- \| \| CBC \| **✔** \|  \| \| LFT \| **✔** \|  \| \| KFT \| **✔** \|  \| \| HBA1C and Blood sugar \| **✔** \|  \| \| RT-PCR for SARS-Cov-2 (until 24hrs apart twice negative) \| **✔** \|  \| \| PT/INR \| **✔** \|  \| \| Serum Electrolytes \| **✔** \|  \| \| ABG \| **✔** \|  \| \| Chest Xray \| **✔** \|  \| \| ECG \| **✔** \|  \| \| Other organ markers as per involvement \| **✔** \|  \|     **Dose Modifications:**  If any serious adverse event is recorded, the participant will be withdrawn from the trial and management will be done accordingly as per institute policy.  **Recording adverse events:**  All adverse events will be recorded in the medical records in the first instance. All adverse events will be recorded with clinical symptoms and accompanied with a simple, brief description of the event, including dates as appropriate. Each adverse event will be assessed for severity, causality, seriousness and expectedness and informed to IEC within 24hours.  **Discontinuation/withdrawal of participants:**  A participant may be withdrawn from trial treatment whenever continued participation is no longer in the participant’s best interests, but the reasons for doing so must be recorded.  Reasons for discontinuing treatment may include:   1. Unacceptable drug toxicity 2. Development of progressive disease 3. Patients withdrawing consent to further trial treatment   **Endpoints:**  **Primary endpoints:**   1. Time to Clinical recovery (TTCR)    - TTCR is defined as the time (in hours) from initiation of study treatment (active or placebo) until normalisation of fever, respiratory rate, and oxygen saturation, and alleviation of cough, sustained for at least 72 hours.    - Normalisation and alleviation criteria: 2. Fever - ≤36.9°C or -axilla, ≤37.2 °C oral 3. Respiratory rate - ≤24/minute on room air 4. Oxygen saturation - >94% on room air 5. Cough- mild or absent on a patient reported scale of severe, moderate, mild, absent 6. Time to SARS-CoV-2 RT-PCR negative in upper respiratory tract specimen 7. Time to laboratory recovery of each organ involvement   **Secondary Endpoints:**   1. All causes mortality 2. Frequency of respiratory progression  - Defined as SPO2≤ 94% on room air or PaO2/FiO2 <300mmHg and requirement for supplemental oxygen or more advanced ventilator support.  1. Time to defervescence (in those with fever at enrolment) 2. Frequency of requirement for supplemental oxygen or non-invasive ventilation 3. Frequency of requirement for mechanical ventilation 4. Frequency of serious adverse events as per AIDS table grade of severity   **Statistical analysis**:  All COVID-19 positive patients will be included in the study after informed consent. Since it is an exploratory trial as COVID-19 being a new disease, all patients who came under the purview of the inclusion criteria within the study period and who have consented for the study will be included. Data will be described as mean+ SD for most of the parameters. Comparisons of the descriptive variables of the two arms will be performed using the Wilcoxon rank sum test for continuous variables and the chi-square or Fisher’s exact test for categorical variables. Primary analysis will include all patients (Intention to treat) and sub-group populations (per-protocol).  **Ethical clearance:**  The present study deals with a new infectious disease which has no definite treatment. Current therapy is based on symptomatic treatment. The present study explores the possibilities of new drugs in SARS-CoV-2 infection. The study will be conducted after IEC approval. Written informed consent will be taken from all participants.  **Safety Outcomes**  Safety outcomes will be determined according to the division of AIDS table for grading severity of adult adverse events (<https://rsc.niaid.nih.gov/clinical-research-sites/daids-adverse-event-grading-tables>), with specific focus on the events of gastrointestinal tract, arrhythmias, myopathies. In case of serious ADRs including death, compensation will be given as per institute protocol. |

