   **Final Clinician’s Impression:**

   **Adverse Event Log**

   | # | Date Reported | Adverse event description | Start Date | End Date | Outcome | Severity/  Grade | AE Treatment | Action Taken | PI Initials | Date of PI Initials |
   | --- | --- | --- | --- | --- | --- | --- | --- | --- | --- | --- |
   |  |  |  |  |  |  |  |  |  |  |  |
   |  |  |  |  |  |  |  |  |  |  |  |
   |  |  |  |  |  |  |  |  |  |  |  |
   |  |  |  |  |  |  |  |  |  |  |  |
   |  |  |  |  |  |  |  |  |  |  |  |
   |  |  |  |  |  |  |  |  |  |  |  |
   |  |  |  |  |  |  |  |  |  |  |  |

   | **Outcome** | **Severity/Grade** | **AE Treatment** | **Action Taken  with Study Intervention** |
   | --- | --- | --- | --- |
   | 0 – Fatal | 1 – Mild | 0 – None | 0 – None |
   | 1 – Not recovered/not resolved | 2 – Moderate | 1 – Medication(s) | 1 – Interrupted |
   | 2 – Recovered w/sequelae | 3 – Severe | 2 – Non-medication TX | 2 – Discontinued |
   | 3 – Recovered w/o sequelae | 4 – Life Threatening |  | 3 – Dose reduced |
   | 4 – Recovering/Resolving | 5 – Death (Fatal) |  | 4 – Dose increased |
   |  |  |  | 5 – Not Applicable |

   [↑](#endnote-ref-1)

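### The serious adverse event endpoint rests on a severity table with no cut-off, and the adverse event log has no field for seriousness, causality or expectedness

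*Protocol*

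**What the plan says.** All references are to the Protocol. Four parts of it bear on this point.

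- **Section (e), Secondary Endpoints.** The endpoint is "Frequency of serious adverse events as per AIDS table grade of severity". No cut-off on the grade is stated.
- **Section (e), Safety Outcomes.** "Safety outcomes will be determined according to the division of AIDS table for grading severity of adult adverse events", "with specific focus on the events of gastrointestinal tract, arrhythmias, myopathies".
- **Section (e), Recording adverse events.** "Each adverse event will be assessed for severity, causality, seriousness and expectedness". Severity and seriousness appear here as two different judgements.
- **Adverse Event Log.** The columns run "Date Reported | Adverse event description | Start Date | End Date | Outcome", then severity/grade, then "AE Treatment | Action Taken | PI Initials | Date of PI Initials". The key grades severity from 1 (mild) to 5 (death).

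Outside the log, the follow-up forms for both strata have one free-text line under Outcomes where serious adverse events can be named. Under Dose Modifications in section (e), a recorded serious adverse event leads to withdrawal of the participant from the trial.

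**The concern.** Severity describes how intense an event is. Seriousness is a separate classification, and the protocol itself lists the two side by side. The endpoint then runs them together by identifying serious events through a severity table, without saying which grade counts.

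Safety is named in the aim and in both objectives, and this is the only adverse event item among the listed endpoints. If its definition is open, assessors can follow the text and still count different patients. The trial is open label. A separate investigator makes the clinical evaluations, but nobody is blinded, so a loosely defined count is exposed to judgements made with knowledge of the arm. The same term also decides who leaves the trial, so the ambiguity reaches retention and the efficacy endpoints.

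A statistical analysis plan could tighten the endpoint definition. It could not supply assessments that the case report form never collects.

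**Working it through.** The protocol states no expected rate of serious events, no sample size (all consenting eligible patients in the study period are taken), no alpha and no power. There is therefore no figure to reproduce, and the check compares text with forms.

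**Step 1. Required assessments against the fields that could hold them.**

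| Assessment required by the text | Adverse Event Log | Follow-up forms, both strata |
| --- | --- | --- |
| Severity | Severity/grade column, codes 1 to 5 | No field |
| Seriousness | No column | One free-text line; no criteria, no reference to a log entry |
| Causality | No column | No field |
| Expectedness | No column | No field |

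On the log, 4 − 1 = 3 of the four assessments have no column. Across all forms shown, 4 − 2 = 2 (causality and expectedness) have no field at all.

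**Step 2. Readings the endpoint wording allows.**

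- (i) Events judged serious, then tabulated by grade.
- (ii) Events of grade 3 or higher.
- (iii) Events of grade 4 or higher.

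Nothing in section (e) rules out any of these.

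**Step 3. How the counts differ.** Within one arm, let *a* be the number of patients with both a serious and a high-grade event, *b* those with a high-grade event but no serious one, and *c* those with a serious event but no high-grade one.

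- Count by seriousness: *a* + *c*
- Count by grade: *a* + *b*
- Difference: (*a* + *b*) − (*a* + *c*) = *b* − *c*

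Even where *b* = *c*, the totals agree but the patients counted are not the same. The comparison between arms shifts whenever (*b* − *c*)/*n* differs between them.

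The documents give no values for *b* or *c*, so the shift cannot be put in numbers. They do show where to expect it. Grades 4 and 5 on the log's key are life-threatening and fatal, where the two ideas largely coincide. Disagreement should come mainly from grade 3 and below. Reading (ii) takes in non-serious grade 3 events, such as a laboratory abnormality, and misses serious events of grades 1 and 2. Reading (iii) misses serious events of grades 1 to 3.

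**Step 4. Withdrawal.** Dose Modifications uses the same term with no definition of its own. A patient with a non-serious grade 3 event would be withdrawn under reading (ii) but not under (i).

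**Step 5. Scope.** The endpoint, the log and the free-text line are the same for the non-severe and severe strata, so the point applies to both.

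**The case against.** **The wording has a milder reading.** It can mean serious events reported by grade, which fits the separate seriousness assessment. That is reading (i), and it may be what was meant. It still leaves seriousness without criteria and without a log column.

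**Seriousness is not wholly uncaptured.** Both follow-up forms have the free-text line, and events go into the medical records in the first instance. This stands, and it is why the point is not that serious events go unrecorded. But the line is not tied to log entries, and no form shown has a structured field for causality or expectedness. The arm boxes on the severe follow-up form also do not list the same three arms as the Treatment Schedule, so arm should be taken from the randomisation record until those passages are reconciled.

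**A reader might infer more: that disease-related events in the severe stratum will overwhelm the safety comparison because of this wording.** The documents do not support that, for these reasons.

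- Life-threatening and fatal disease events would ordinarily count as serious too, so disease background reduces sensitivity under any definition of a serious event.
- Entry conditions such as ventilation or septic shock are baseline states, and nothing says they are logged as adverse events.
- The randomised standard-treatment arm means a background common to all arms does not by itself create a false difference.
- A power calculation would need event rates, a background rate and an arm size, all assumed. Set against a reference with no disease events, it would measure the effect of enrolling sick patients, not of this wording.

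**Nor does the protocol call this its main safety comparison.** It is the last-listed secondary endpoint. All-cause mortality is separate, and attention is also directed to gastrointestinal, arrhythmic and muscle events.

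**Conclusion.** The point holds as a defect of definition and data capture. The endpoint ties seriousness to a severity table without a cut-off, against the protocol's own separation of the two. Three of the four required assessments have no column on the log, and two have no field on any form shown. The count of serious events by arm can therefore include high-grade non-serious events and miss serious low-grade ones, in both strata, and the withdrawal rule inherits the ambiguity. Section (e) and the Adverse Event Log must be reconciled.

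The size in events or power is unknown and cannot be derived from the protocol. The conclusion rests on the ordinary distinction between severity and seriousness, which the protocol itself draws, and on the forms shown being the complete case report form. It should be corrected, but it does not undermine the trial as a whole.

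**What to change.** 1. Define the endpoint as the proportion of patients with at least one event judged serious under the assessment already required, and write out the criteria used. Counting patients also suits the chi-square or Fisher's exact test named under Statistical analysis.
2. Report separately the proportion of patients with at least one new or worsened event of grade 3 or higher by the cited table. The words new or worsened make explicit that conditions present at entry are not counted.
3. Add columns for seriousness, causality and expectedness to the Adverse Event Log, and link each entry on the follow-up forms' serious event line to its log entry.
4. Compare all events between randomised arms regardless of attribution. Use causality as supportive information only, since attribution in an open-label trial can itself be biased.
5. Make the term used in the withdrawal rule consistent with the definition adopted. What that rule should be is for the investigators.

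The cost is a rewording, three log columns, slightly more form-filling and one extra safety table. The assessments are already required, so no patient procedure is added. The change is best made before data collection, because causality and expectedness are hard to reconstruct later.

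### Three unranked primary endpoints, one of them open-ended, and two analysis sets both called primary leave no single result that answers either objective

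*Protocol*

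**What the plan says.** All of this is in item (e) of the protocol's brief description of the proposal, except the objectives, which are in item (b).

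- **Endpoints.** The primary list holds time to clinical recovery (TTCR), "Time to SARS-CoV-2 RT-PCR negative in upper respiratory tract specimen" and "Time to laboratory recovery of each organ involvement". No order is given. The four criteria that define clinical recovery are numbered in the same list, so the numbering runs to 7, but there are three endpoints. The number of organs is not fixed.
- **Another headline.** The outcomes line at the start of item (e) names something else: "Clinical and laboratory improvements in 72 hours of treatment".
- **Arms and comparisons.** There are "Two therapeutic interventions for non-severe category and three for severe category as described below", and arms are "compared among other interventional arm in same category". Item (b) has one objective for the non-severe group and one for the severe group. The severe objective names three regimens and no lead contrast.
- **Analysis sets.** "Primary analysis will include all patients (Intention to treat) and sub-group populations (per-protocol". Neither set is put first, and the per-protocol set is not defined.
- **Leaving assigned treatment.** Severe-group non-responders move to the institute's own protocol. Non-severe patients who fail to improve are re-randomised in the severe group with new consent. Progressive disease and unacceptable toxicity are reasons to discontinue, and a serious adverse event leads to withdrawal from the trial.
- **Status.** Item (e) calls the trial exploratory, twice. It states no sample size, significance level or success rule.

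**The concern.** A reader of the results needs to know which one answers each objective. Here there are several candidates of equal rank. Two problems follow.

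First, each added primary endpoint gives another chance of a nominally positive primary result when no drug works. The organ endpoint makes the number of chances indefinite. It also exists only for patients with organ involvement, so it is not an endpoint in all randomised patients.

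Second, the two primary sets can disagree. Patients come off assigned treatment because of how they fare, so a set selected on staying on treatment is selected partly on outcome. Drug toxicity can remove patients only from the arms that receive the study drugs, so such selection need not be equal across arms. A per-protocol result presented as primary could then show a difference that randomisation does not support.

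**Working it through.** The protocol gives no error rate or power figure to reproduce. The check counts the tests the text implies and finds the chance of at least one false positive when no drug has any effect.

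**Inputs from the protocol**
- Primary endpoints: 3, counting organ recovery once.
- Arms: 2 non-severe, 3 severe.
- Pairwise comparisons within a category: 1 + 3 = 4. This count is derived from the comparator line; the protocol does not list it.

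**Assumptions**
- Two-sided 5% per test.
- Equal arm sizes, approximately normal test statistics, and severity groups treated as independent.
- Correlation between endpoints from 0 to 0.7.

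**Test counts**
- Non-severe: 3 × 1 = 3. Severe: 3 × 3 = 9. Both: 12.

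**Bound if all tests were independent**, 1 − 0.95^k
- k = 3: 14.3%. k = 9: 37.0%. k = 12: 46.0%.

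**Simulation allowing for shared arms and correlated endpoints** (intention-to-treat only)

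| Endpoints | Correlation | Non-severe | Severe | Either |
| --- | --- | --- | --- | --- |
| 3 | 0 | 14% | 32% | 42% |
| 3 | 0.3 | 14% | 31% | 40% |
| 3 | 0.5 | 13% | 28% | 37% |
| 3 | 0.7 | 11% | 25% | 33% |
| 1 | n/a | 5% | 12% | 17% |

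The one-endpoint row has no multiplicity adjustment. Holm over the three severe comparisons would bring the 12% to at most 5%, and the chance over both objectives to at most 5% + 5% = 10%.

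**Adding what the table leaves out**
- Per-protocol as a second primary set: 12 × 2 = 24 tests. With an assumed correlation of 0.7 to 0.9 between the sets, the chance over both objectives is 43-60%.
- If the organ endpoint meant three organs (an assumption): 5 endpoints × 4 = 20 tests in intention-to-treat, giving 42-60%.

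**Per-protocol illustration.** Assume 60% recovery in every arm and no drug effect. If half of one arm's non-recovered patients are excluded, its apparent recovery is 0.60 / (1 − 0.40 × 0.5) = 0.60 / 0.80 = 75%. The exclusion rate is hypothetical; it shows the direction and possible size of the bias.

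**The case against.** **The trial is exploratory, and a SAP may exist.** Familywise error control is mainly a demand on confirmatory claims, and a multiplicity method or a per-protocol definition is commonly left to the SAP. This stands, so the absence of either is not counted as a fault here. But the protocol does choose its primary endpoints and primary sets, and it chooses several without rank. A SAP that named one would have to depart from this text.

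**The number of tests is constructed.** The severe objective could be met by one overall three-arm test. The only test sentence, "Comparisons of the descriptive variables of the two arms will be performed using the Wilcoxon rank sum test for continuous variables", concerns descriptive variables and two arms. This also stands: all pairs is a plausible reading of the comparator line, not the only one. The non-severe count of three does not depend on it.

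**A reader might infer that a chance finding is likely.** The figures do not support that for intention-to-treat with three endpoints: 33-42% over both objectives is below one half and rests on an assumed 5% per test. The risk is raised several-fold for the severe objective and two- to threefold for the non-severe one.

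**A reader might infer that the per-protocol set drops treatment failures.** The documents do not say so, because the set is undefined. A severe-group patient shifted for progression is following the protocol, and the flow diagram counts that patient as having reached an endpoint, so such a patient could be kept. The set may drop failures; it need not.

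**Making per-protocol supportive does not cure every loss.** If withdrawal after a serious adverse event also ends follow-up, intention-to-treat loses those data too. That is true and needs separate attention.

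**TTCR is not the obvious lead.** The trial is open label and TTCR includes patient-reported cough, whereas RT-PCR is more objective. The documents favour neither, so the choice belongs to the investigators.

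**Conclusion.** The point holds. The protocol gives primary status to at least three unranked endpoints, one with no fixed number of components, and to two analysis sets with no rule if they conflict. An undefined per-protocol set may exclude treatment failures, possibly unequally by arm, and should not carry primary status.

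Under the assumptions listed, three endpoints instead of one raise the chance of a false-positive primary result from 5% to 11-14% for the non-severe objective, and from about 12% to 25-32% for the severe objective. These figures cover intention-to-treat alone and count the organ endpoint once; further organs or the second set would raise them.

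The analysis-set point needs no assumption about test counts or significance level. The multiplicity point is softer because the trial calls itself exploratory. The change should be made, but the defect does not invalidate the design.

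**What to change.** 1. State that intention-to-treat is the sole primary analysis set for both objectives and that per-protocol is supportive.
2. Have the investigators name one lead primary endpoint for each objective, or a fixed testing order. TTCR is listed first and is the natural candidate, but RT-PCR negativity could be defended.
3. Move organ laboratory recovery to the secondary endpoints.
4. In the severe group, do one of three things: name the lead contrast, apply Holm over the three pairwise comparisons, or report all three as exploratory without significance claims.

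**Cost.** The edits are to wording; enrolment, visits and treatment do not change. With a single lead endpoint, two endpoints lose primary status. If Holm is used, the smallest severe-group p-value is multiplied by 3, so 0.03 becomes 0.09. That is a real loss of power in a group with no planned sample size, and a reason to consider a named lead contrast instead.
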